**Patient population 2**					
*Diagnosis*					
Mini-International Neuropsychiatric Interview (M.I.N.I.)		+			
Sheehan Suicidality Tracking Scale (S-STS)		+			
*Demographic and disease characteristics*					
Age		+			
Sex		+			
Body Mass Index (BMI)		+			
Family psychiatric disorders		+			
Education, employment		+			
Referral context		+			
ICD-10 F-Diagnosis		+			
Depressive episode (number, duration)		+			
Suicidality (current, lifetime)		+			
Psychiatric emergency (admission, current)		+			
Current and previous treatment (medication, psychotherapy, inpatient, electroconvulsive therapy)		+			
Treatment-resistant depression		+			
Medication nonadherence		+			
Substance use		+			
**Patient population 3 (M.I.N.I. + S-STS validated)**					
*Psychopathology, suicidality, comorbidity, stressors*					
Montgomery-Asberg Depression Rating Scale (MADRS)		+	+	+	+
Sheehan Suicidality Tracking Scale (S-STS)			+	+	+
Clinical Global Impression—Change (CGI-C)		+	+	+	+
Clinical Global Impression—Severity (CGI-S)		+	+	+	+
Clinical Global Impression of Imminent Suicide Risk (CGI-SR-I)		+	+	+	+
Clinical Global Impression of resolution of Suicide Risk (CGI-SR-R)		+	+	+	+
Mini-International Neuropsychiatric Interview (M.I.N.I.)					+
ICD-10: Borderline criteria checklist		+			
Young Mania Rating Scale (YMRS)		+	+	+	+
Personal and Social Performance Scale (PSP)		+	+	+	+
Previous and current substance use		+	+	+	+
Psychiatric emergency (since last visit, current)			+	+	+
*Self-ratings*					
Quick Inventory of Depressive Symptomatology-Self Report [QIDS-S]^38^		+	+		+
Beck Depression Inventory—II (BDI-II)		+	+		+
Beck Anxiety Inventory (BAI)		+	+		+
Quality of Life in Depression Scale (QLDS)		+	+		+
European Quality of Life Group, 5-Dimension, 5-Level (EQ-5-DL)		+	+		+
36-item Short-Form Health Survey (SF-36)		+	+		+
Work Productivity and Activity Impairment (WPAI)		+	+		+
Patient Health Questionnaire 9-item (PHQ-9)		+	+		+
Beck Hopelessness Scale (BHS)		+	+		+
Munich Chronotype Questionnaire (MCTQ)		+	+		+
State -Trait Anger Expression Inventory (STAXI)		+	+		+
Aggression Questionnaire—Buss Perry (AF-BP)		+	+		+
*Utilization of health services*					
Service Use and Resource Form (SURF)		+		+	+
Documentation of clinical routine and treatment (both outpatient and inpatient) - Medication (including reason for initiation, discontinuation and switching, effectiveness and safety - Electroconvulsive therapy		+	+	+	+
*Physical examination and side effects*					
Body Mass Index (BMI)		+	+		+
Adverse side effect of medication		+	+	+	+
*Adherence*					
Questionnaire for recording adherence		+	+	+	+

### Sample size and statistical analyses

Regarding PP1, the projected number of approximately *n* = 3,000 of the epidemiologic sample of hospitalized patients with MDD in the included age range (18–75 years) is based directly on the number of these patients in the eight participating study centers that were sampled in preparation of the study in 2017. Since only descriptive results are analyzed for patient population 1, no formal power analysis and case number calculation are provided. Descriptive statistics will be used to characterize a systematically and consecutively included epidemiologic sample of patients with MDD. Two interim analyses are performed using the same described descriptive statistics in PP1 at the epidemiologic sample size time points of 500 and 2000, respectively. These interim analyses are performed to identify potential data gaps and opportunities for the participating centers to review and address data capture and recording procedures of routine clinical information relevant to the characterization of patients hospitalized with MDD. Due to a higher observed patient dropout (30–35%) in PP3 between discharge and 6-month follow-up than projected in the initial protocol (20%), the subject number in PP3 was increased (see below) and the study duration was extended, which also provides more time for recruitment of patients into PP1, i.e., until the date of the last assessment of the last patient in PP3, increasing the projected number of patients to approximately *n* = 4500.

The hypotheses pertaining to PP1 will be analyzed exploratorily by using appropriate descriptive statistics, as well as univariate tests (chi-square tests).

Regarding PP2, based on clinical experience and questionnaire information from the recruitment centers as part of the design preparations, an estimated 33% of 3331 patients (*n* = 1,099) with a clinical diagnosis of at least moderately severe MDD are assumed to be still suicidal ≥ 48 h after admission. Approximately 60% of this group are expected to consent to participate in the interview-based study (and the naturalistic, 6-month follow-up study, should they also fulfill criteria for PP3, determined during participation in PP2). The following analyses of congruence between clinical diagnosis and research diagnosis (gold standard) of at least moderately severe MDD will take place:(a) two groups will be formed (primary analysis), i.e., positive vs. negative validation of the clinical diagnosis with the research-based interview M.I.N.I.,(b) use of descriptive statistics to estimate proportions of patients meeting the gold standard of research diagnosis and their confidence intervals (see a, hypothesis 2A), as defined by diagnostic concordance with the clinical diagnosis at the time of hospitalization; and.(c) to perform multiple mixed logistic regression analysis with backward elimination to compare patients with positively validated and non-validated at least moderately severe MDD (see a, hypothesis 2B), with random factors to account for clustering of patients in centers.

Regarding PP3, the OASIS-D study was initiated with the assumption that approximately 50% of the 520 patients surveyed in PP2 would not meet ICD-10 criteria for the inclusion criteria of at least moderately severe MDD, so that260 patients would be enrolled in PP3. Assuming a 20% drop out rate, this would yield n = 208 with data at 6 months. During the interim analysis 2, in September 2022, we noted a higher drop-out rate of 34% in PP3 than the 20% expected attrition rate at the time of the study design. Due to this finding, the number of patients in PP3 was increased to n = 315, so that with an attrition rate of 34%, the number of patients with data at month 6 would remain at n = 208. Since there was a higher than initially projected transition rate from PP2 to PP3, so that the n of patients entering PP2 did not need to be increased.

Hypotheses 3A and 3C will be analyzed by means of methods for count data, such as Poisson or Negative Binomial models, depending on whether overdispersion is present in the data or not. The dependent variable will be overall duration of PASI during the 6-month observation period and the independent variable of main interest will be time to remission of suicidal symptoms after baseline.

Hypotheses 3B and 3D will be analyzed by using Cox proportional hazard models, where the dependent variable will be time-to-first-recurrence of PASI and the independent variable of main interest will be time to remission of suicidal symptoms after baseline.

Further independent variables for regression analysis will include patient, illness, and treatment variables, including severity of depressive symptoms (MADRS, Quality of Life in Depression Scale (QIDS-S) [79]), manic symptoms (YMRS), anxiety (BAI), anger/hostility (STAXI, AF-BP), global illness symptoms (CGI-S), quality of life (EQ-5-DL), and suicidality (S-STS); presence of psychiatric emergencies; number of lifetime depressive episodes; duration of current depressive episode; nonadherence to pharmacological and nonpharmacological treatments; and comorbid borderline personality and substance abuse. Additionally, a random factor accounting for clustering of patients in centers will be added to the models.

Assuming a minimum requirement of 10 patients per predictor variable in regression analyses [91–93] and approximately 20 independent patient, illness, and treatment variables that would be tested as potential correlates of time to remission of suicidality, we estimated that a sample size of at least 200 would be required.

Additionally, as a secondary analysis, we will divide patients into two groups using the median time up to the first S-STS value of zero, which are either below or above the median time to first complete remission of suicidality.

Furthermore, comparisons between the slower and faster remitting group of continuous variables will be performed using multiple comparison procedures (MCPs) with 3 measurement time points (T1, T2, and T4). Because only the primary outcome and very limited other parameters are collected by telephone at T3, data at T3 are not included in these analyses. Because the timing at T2 (hospital discharge) is variable, and this timing is not independent of the outcome measured, the duration between T1 and T2 is included as a covariate in the analyses. Cross-group comparisons of dichotomized or categorical variables are performed using chi-square statistics. For ease of comparison, continuous outcomes, such as depressive symptoms and medication use are calculated. All analyses are two-sided, with alpha = 0.05. Due to the exploratory nature of the study, no adjustment for multiplicity between different endpoints is conducted. Hence, p-values and confidence intervals need to be interpreted in a hypothesis-generating manner. In addition, multivariable regression analysis with backward selection will be performed to identify independent moderators or mediators of continuous and categorical outcomes, respectively. Moreover, missing continuous data will be treated using multiple imputation using chained equations and random effects for the clustering of patients in different centers.

Among the exploratory objectives, the patient, illness, and treatment factors that influence the risk of different levels of active suicidality are identified: i) active suicidality (S-STS item 3), ii) active suicidality with preparatory action (S-STS item 12), iii) self-injurious behavior without suicidal intent (S-STS item 13), and iv) suicide attempt (S-STS item 14) during the observation period of inpatient treatment and within 6 months of study inclusion (T1). Target parameters i)-iv) are associated with slower initial resolution of suicidality (lower than median time to S-STS score = 0); and with: Depressive symptom severity (MADRS, QIDS-S), manic symptoms (YMRS), anxiety (BAI), anger/hostility (STAXI, AF-BP), and global illness symptoms (CGI-S); higher number of lifetime depressive episodes; more frequent psychiatric emergencies; longer duration of current depressive episode; non-adherence to pharmacological and non-pharmacological treatments; comorbid borderline personality; and substance abuse diagnoses.

All analyses will be performed as intent-to-treat analyses, independent of non-adherence with clinically prescribed treatments or drop out from clinical care.

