### Primary inclusion criteria

Inclusion criteria for PP1 are (i) male and female patients; (ii) aged between 18 and 75 years; (iii) admitted to a psychiatric inpatient unit, and (iv) having an ICD-10-based chart diagnosis of single depressive episode (F32) or recurrent depressive episode (F33).

Inclusion criteria for PP2 (originating from PP1) are (i) male and female patients; (ii) aged between 18 and 75 years; (iii) admitted to a psychiatric inpatient unit; (iv) having an ICD-10-based *clinical* diagnosis of a single or recurrent depressive episode of *at least moderate severity*, including single depressive episode, moderate episode (F32.1), single depressive episode, severe episode without psychotic symptoms (F32.2), single depressive episode, severe episode with psychotic symptoms (F32.3), recurrent depressive episode, currently moderate episode (F33.1), recurrent depressive episode, currently severe episode without psychotic symptoms (F33.2), and recurrent depressive episode, currently severe episode with psychotic symptoms (F33.3); (v) *clinically* diagnosed suicidality that persists for ≥ 48 h after inpatient admission; and (vi) sufficient German language skills to understand the purpose and procedures of the study and cooperate with the study procedures; and (vii) providing written informed consent to participate in the study.

Inclusion criteria for PP3 (originating from PP2) are (i) male and female patients; (ii) aged between 18 and 75 years; (iii) admitted to a psychiatric inpatient unit; (iv) having an ICD-10-based *research* diagnosis according to the Mini-International Neuropsychiatric Interview (M.I.N.I.) [71] of a single or recurrent depressive episode of *at least moderate severity* (for details, see PP2 above); (v) *research interview-based* suicidality with a score ≥ 1 on item 2 (passive suicidality) OR item 3 (active suicidality) using the Sheehan–Suicidality Tracking Scale (S-STS) [21]; (vi) written informed consent to participate in the study.

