### Aims and hypotheses

The primary aim in PP1 is to systematically characterize patient, illness, and treatment characteristics of consecutively admitted patients with a clinical diagnosis of a single or recurrent unipolar depressive episode.

#### Hypothesis 1

We hypothesize that MDD at inpatient admission is characterized by (i) most frequent referral by a primary care physician, (ii) female patient predominance of about 60% [5, 6], (iii) older patients aged approx. 45 years [5, 6], (iv) admission due to psychiatric emergency in approx. 25% of the sample, (v) occurrence of treatment-resistant depression in approx. 20% of the sample [11], (vi) occurrence of at least passive suicidal ideation in at least 50% of the sample [6, 72], (vii) lifetime history of a suicide attempt in approx. 20% of the sample [14], and (viii) preponderance of medication treatment with selective serotonin reuptake inhibitors (SSRIs) [9, 10].

#### Hypothesis 2

The primary aim in PP2 is to test the validity of the clinical diagnosis of at least moderately severe MDD in patients with clinically documented suicidality using the M.I.N.I. and compare predictors (diagnosis, demographic and illness characteristics, treatment) between patient groups with concordant and discordant clinical and research diagnosis.

Hypothesis 2A: We hypothesize that in < 50% of patients the clinical diagnosis will not be confirmed by the structured research diagnosis [38].

Hypothesis 2B: We hypothesize that the patient group with unvalidated vs validated clinical diagnosis of at least moderately severe MDD by the research interview compared will be associated with (i) younger age (less historical information and more dynamic emergence of (co)morbidities) [39], (ii) female sex (possible diagnostic bias), (iii) lower number of previous depressive episodes (less historical validation), (iv) lower number of index admission in the context of a psychiatric emergency (less historical validation), (v) higher number of comorbid personality disorders (more diagnostic overlap) [40, 41], and (vi) lower suicidal severity (less severe psychiatric condition).

#### Hypothesis 3

The primary aim of PP3 is a 6-month structured recording of the duration and frequency persistence and recurrence of suicidality and its correlates in 315 patients diagnosed with at least moderately severe MDD by the M.I.N.I. and with confirmed presence of at least passive suicidal ideas by the S-STS ≥ 48 h after inpatient admission.

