### Assessments and timeline

In PP1, sociodemographic, family, illness, and treatment-related data are collected to characterize patients with MDD at the time of inpatient admission (T0), i.e., age (coded in 5 year intervals), sex, ICD-10 F-diagnosis, current and lifetime suicidality, psychiatric emergencies, current and previous treatments, medication resistance, and nonadherence.

In PP2, sociodemographic, illness and treatment data (i.e., sex, Body-Mass-Index (BMI), family psychiatric disorders, education/ work, pathways to admission, F-diagnosis of ICD-10, illness duration, number of episodes, current and lifetime suicidality, psychiatric emergency, current and previous treatment, medication treatment-resistance and non-adherence, substance use) are collected at ≥ 48 h after inpatient admission (T1). M.I.N.I. will be used as an interview to determine the research diagnosis of at least moderately severe MDD, and S-STS will be used to assess suicidality.

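### The PP2 validity analysis compares an admission diagnosis with a later M.I.N.I. on a severity threshold, so true improvement before T1 can be counted as non-validation

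*Protocol article*

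**What the plan says.** All references are to the protocol article.

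- **Diagnosis under test.** Sample size and statistical analyses (PP2) estimates the proportion meeting the research diagnosis, "as defined by diagnostic concordance with the clinical diagnosis at the time of hospitalization".
- **Reference test and its time.** Under Assessments and timeline, "M.I.N.I. will be used as an interview to determine the research diagnosis of at least moderately severe MDD". The PP2 data "are collected at ≥ 48 h after inpatient admission (T1"), and Table 1 places the M.I.N.I. at T1.
- **Threshold.** The criterion is depression of at least moderate severity. Primary inclusion criteria lists the qualifying codes, and those for recurrent illness describe the present state, for example "recurrent depressive episode, currently moderate episode (F33.1"). The research diagnosis for PP3 refers back to this list.
- **Outcome groups.** "two groups will be formed (primary analysis), i.e., positive vs. negative validation of the clinical diagnosis with the research-based interview M.I.N.I". No third category exists.
- **Hypotheses.** 2A expects that "in < 50% of patients the clinical diagnosis will not be confirmed by the structured research diagnosis". 2B expects the unvalidated group to show, among six features, "lower suicidal severity (less severe psychiatric condition").
- **Timing elsewhere.** For PP3, the same statistics section says that discharge timing varies and is not independent of the outcome, and it makes the T1–T2 duration a covariate. It states no such term for the interval from admission to T1 in PP2.

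**The concern.** The two diagnoses refer to different moments, and what is compared can change between them. A patient may have had a moderate episode at admission, correctly diagnosed, and a mild one at T1 after some days of inpatient care. Under a two-group rule that patient can only fall into negative validation, together with patients whose admission diagnosis was wrong.

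Two results are exposed. The 2A rate would understate the validity of the admission diagnosis. In 2B, a variable related to early improvement could appear as a predictor of an unvalidated diagnosis. Suicidal severity is the clearest candidate: the S-STS is given at T1 alongside the M.I.N.I., so a patient who has improved may score lower on both. The planned confidence intervals would show none of this, since they reflect sampling error only.

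**Working it through.** **1. The plan's own figures.** 520 × 0.50 = 260 entering PP3; 260 × 0.80 = 208 at month 6. With 34% attrition, 208 / 0.66 = 315.2, which rounds up to 316; the plan uses 315 (315 × 0.66 = 207.9). The chain reproduces. If PP2 stays near 520, 315 entrants imply at least 315/520 = 60.6% confirmed, hence at most 39.4% unconfirmed.

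**2. Model for the 2A rate.** Let d be the true non-confirmation at admission and q the share of correctly diagnosed patients who are truly below moderate by T1 and are rated so. Then

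observed non-confirmation = 1 − (1 − d)(1 − q).

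The documents give neither d nor q. Both are assumptions here, with q taken from 5% to 20%.

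| True d | q = 5% | q = 10% | q = 20% |
|---|---|---|---|
| 30% | 33.5% | 37.0% | 44.0% |
| 35% | 38.3% | 41.5% | 48.0% |
| 45% | 47.8% | 50.5% | 56.0% |

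**3. Against sampling error.** At d = 35% and n = 500, the 95% half-width is 1.96 × √(0.35 × 0.65 / 500) = 4.2 points. The shifts at q = 5%, 10% and 20% are 0.65 × q = 3.25, 6.5 and 13 points. The first lies within the half-width and the other two exceed it. The shift equals the half-width at q = 4.2/65, about 6.4%.

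**4. Share of the unconfirmed group that is improvement.** At d = 35%: 6.5/41.5 = 16% for q = 10%, and 13/48 = 27% for q = 20%. Most discordance is still real in the largest case assumed.

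**5. Direction for 2A.** Improvement adds to non-confirmation, so it pushes the rate towards 50%, away from the hypothesis. Only a true rate already close to 50% would cross: at d = 45%, crossing needs q above 1 − 0.50/0.55 = 9.1%. Working back from 39.4% observed, the true rate, 1 − 0.606/(1 − q), would be 36.2%, 32.7% or 24.3% for q = 5%, 10% or 20%.

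**6. Effect on 2B odds ratios (assumed values).**

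- *Improvement unrelated to the predictor.* Take discordance of 25% in the reference group and a true odds ratio of 2.0, so 40% in the other group. At q = 10% these become 32.5% and 46.0%, and the odds ratio is (0.46/0.54)/(0.325/0.675) = 1.77. At q = 5% and 20% it is 1.87 and 1.63.
- *Improvement related to the predictor.* Take true discordance of 30% in both groups, with q = 5% in one and 15% in the other. Observed discordance is 33.5% and 40.5%, and the odds ratio is (0.405/0.595)/(0.335/0.665) = 1.35 where the true value is 1.0.

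**The case against.** - **Early improvers are partly screened out.** PP2 requires clinically diagnosed suicidality persisting at 48 h or later, a rule the trial design section explains as removing transient cases. This stands as a limit on size. It should lower q, but it does not exclude a fall in depressive severity while suicidal thoughts persist.
- **The look-back of the M.I.N.I. is not stated.** If it covers the day of admission, a short delay does little harm. This stands for short delays and less so for long ones.
- **A latest time for T1 may exist.** A reader might infer from the article that interviews can happen at any point of the stay. That cannot be held against the plan: an interview window is the sort of detail an article leaves to the full protocol. The mismatch exists at any delay, but its importance depends on a delay distribution that is not given.
- **Overcalled severity is genuine discordance.** The stated aim is the validity of a moderate or severe diagnosis, so a case that was mild at admission is rightly unvalidated. This stands. It would be wrong to count only patients with no depressive episode as misdiagnosed.
- **The 2B mechanism is possible, not shown.** No section says that suicidal severity or admission type predicts early improvement, and 2B does not date its suicidal severity measure; suicidality is recorded at admission as well.
- **The study calls itself exploratory**, with p-values and intervals to be read as hypothesis-generating. That lowers the stakes but does not remove a bias in an estimated rate.

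**Conclusion.** The point holds in a limited form. As written, the comparison lets true change between admission and T1 count as failed validation, and the stated PP2 analyses have no means of separating the two. The size cannot be derived from the documents. Under the assumed 5% to 20%, the shift in the 2A rate at 35% true non-confirmation runs from 3.25 to 13 points, and the persisting-suicidality rule argues for the lower part of that range or below it.

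Two stronger readings are tempting and are not supported. A reader might infer that PP2 would measure who improved early and not whose diagnosis was invalid. Even at 20%, improvers make up 13 of 48 points of discordance. A reader might also infer that the bias could produce a favourable 2A result. It works the other way: if 2A is supported, this bias cannot be the reason. What is at risk is the accuracy of the reported rate and the reading of 2B predictors measured at T1.

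**What to change.** Keep the two-group primary analysis. Add a pre-specified sensitivity analysis with two parts:

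1. Split non-validated cases into those with no unipolar depressive episode and those with an episode present but below moderate at T1, and report 2A and 2B for each. The second group mixes overcalled severity with improvement and should be described that way, not treated as correctly diagnosed.
2. Tabulate concordance by days from admission to M.I.N.I., and add that interval as a fixed covariate in the 2B mixed logistic model, held in regardless of backward elimination. This parallels the T1–T2 covariate already planned for PP3. It does not correct the misclassification; it shows whether non-validation varies with delay.

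Table 1 also lists an "ICD-10 F-Diagnosis" for PP2 at T1. Use it as a same-time comparator only if it is a fresh clinical rating. The article does not say so, and it may be the admission diagnosis carried forward.

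Cost: no new visit, one extra model term, and smaller groups in the split. With about 520 in PP2 and 315 confirmed and enrolled, at most 520 − 315 = 205 non-validated cases would be divided between the two types, so the split 2B results will be imprecise. The admission date is not listed in Table 1, but the 48 h rule needs it. The sponsor should confirm that the date, and whether an episode was present and at what severity on the M.I.N.I., are kept in the database.

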Hypothesis 3A: We hypothesize that the time to remission of suicidal symptoms after the baseline is a major determinant of shorter overall duration of passive or active suicidal ideation (PASI) during the entire 6-month observation period.

Hypothesis 3B: We hypothesize that the rate of remission of suicidal symptoms after baseline is a major determinant of lower recurrence of PASI during the 6-month observation period.

Hypothesis 3C and 3D: We hypothesize that a longer total duration of PASI (Hypothesis 3C) and a greater risk of recurrence of PASI after complete remission (Hypothesis 3D) during the 6-month observational phase is associated with the following factors at time T0 (i.e., “moderators”): greater severity of (i) depressive symptoms [28, 36, 42, 43], (ii) manic symptoms (below the threshold of (hypo)mania as part of MDD), (iii) anxiety symptoms [28, 36, 45], (iv) anger and hostility [43], (v) quality of life impairment [48, 49], (vi) global symptoms of illness and (vii) suicidality [28, 36, 42, 47], (viii) higher number of lifetime depressive episodes, (viii) index admission as part of a psychiatric emergency, (ix) longer duration of current depressive episode [44], (x) higher non-adherence to pharmacological and non-pharmacological treatments, (xi) comorbid borderline personality disorder [35, 46], and (xii) comorbid substance use diagnosis [28].

Exploratory study aim 1 of PP3 is to describe the association between PASI and suicide attempts (S-STS item 14) as well as with the utilization of outpatient and inpatient care services during the 6-month observation period.

Exploratory hypothesis 1A, 1B and 1C: We hypothesize that a higher number of days with PASI (exploratory hypothesis 1A), a higher number of days with active suicidal ideation (exploratory hypothesis 1B) and a higher number of suicide attempts (exploratory hypothesis 1C) during the 6-month observation period are significantly associated with a higher number of (i) outpatient appointments, (ii) emergency department visits, (iii) inpatient hospitalizations, (iv) hospitalizations as part of psychiatric emergencies, (v) psychiatric hospital bed days, and (vi) suicide-related hospital bed days.

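### Hypotheses 3C and 3D share models with time to remission, so 3C in particular would be tested conditional on a post-baseline intermediate that is also part of its outcome

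*Protocol article*

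**What the plan says.** In the protocol article, *Sample size and statistical analyses* pairs the four PP3 hypotheses by model.

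- **3A and 3C:** "Hypotheses 3A and 3C will be analyzed by means of methods for count data", with Poisson and negative binomial models named as examples. The outcome for both is total PASI duration over the six months, and the main regressor is time to remission counted from baseline.
- **3B and 3D:** "Hypotheses 3B and 3D will be analyzed by using Cox proportional hazard models". The dependent variable is "time-to-first-recurrence of PASI and the independent variable of main interest will be time to remission of suicidal symptoms after baseline".
- **Baseline factors:** "Further independent variables for regression analysis will include patient, illness, and treatment variables". The list that follows covers depressive, manic, anxiety and anger scales, global severity, quality of life, suicidality, emergencies, episode history, non-adherence and comorbidity. These are the factors of 3C and 3D. A centre random factor is then added to the models.

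No model for 3C or 3D without time to remission is described. Later in the same section, an additional multivariable regression with backward selection is planned to find moderators or mediators; it does not say whether time to remission is among the candidates.

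Under *Aims and hypotheses*, 3C (total PASI duration) and 3D (recurrence after complete remission) each say that the outcome "is associated with the following factors at time T0". Neither is conditional on time to remission.

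**The concern.** 3C asks whether patients who start out more severely ill, more anxious or with more comorbidity go on to have more days of PASI. The model given for it holds time to remission fixed. That variable arises after the factors are measured, and the article itself places it on the path: 3A and 3B make remission a main driver of the two outcomes, and the sample-size paragraph treats about 20 patient, illness and treatment variables as possible correlates of time to remission. Holding it fixed changes the question to whether the factor matters among patients who remitted equally fast.

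For 3C there is also a structural overlap, since days up to first remission are themselves days counted in the outcome. A factor that prolongs suicidality by delaying remission could then show little or no association in the very model assigned to 3C. Finding such patients is a stated purpose of the study.

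A smaller inconsistency sits alongside. The factors are placed at T0, but Table 1 has no T0 value for the rating scales.

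**Working it through.** **1. The plan's own figures.** 10 patients per predictor × about 20 predictors = 200. 260 × (1 − 0.20) = 208. 315 × (1 − 0.34) = 207.9; in reverse, 208 / 0.66 = 315.2, which rounds up to 316 against the stated 315. These reproduce. They do not test the present point, which concerns model content, and they do not change if one regressor is removed.

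**2. Structure of the 3C outcome.** Let R be days from T1 to first remission and L the PASI days after it. If ideation is continuous until first remission, total PASI days are Y = R + L. With R in the model, a baseline factor X can explain only what it adds through L at a given R. If ideation fluctuates before remission the identity loosens, but R and Y still overlap heavily.

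**3. Structure of the 3D outcome.** The article gives no time origin for time to first recurrence. If the clock starts at remission, R is an intermediate but not part of the outcome. If it starts at baseline, R is part of the outcome as well.

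**4. Illustration.** All inputs here are assumptions except n = 208, which is the article's month-6 number, and the two-sided alpha of 0.05. X is standardised. R is exponential with mean 40·exp(bX) days, capped at 182. Time from remission to recurrence is exponential with mean 120·exp(−[gX + d(log R − 3.2)]) days. There is at most one later episode, of mean length about 20 days. 3C is fitted as quasi-Poisson and 3D as Cox with the clock starting at remission, each with and without R. There were 300 runs per row, no centre effect and no other covariates. Brackets give the share of runs with p < 0.05.

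| b, g, d | 3C RR without R | 3C RR with R | 3D HR without R | 3D HR with R |
|---|---|---|---|---|
| 0.2, 0, 0.4 | 1.146 (72%) | 0.995 (3%) | 1.041 (7%) | 0.991 (5%) |
| 0.3, 0, 0.4 | 1.225 (96%) | 1.001 (5%) | 1.077 (12%) | 1.000 (4%) |
| 0.5, 0, 0.4 | 1.379 (100%) | 1.015 (8%) | 1.126 (26%) | 0.997 (6%) |
| 0.3, 0, 0 | 1.209 (98%) | 1.002 (6%) | 0.994 (6%) | 0.993 (7%) |
| 0.3, 0.2, 0.2 | 1.249 (99%) | 1.031 (14%) | 1.266 (79%) | 1.224 (67%) |
| 0, 0, 0.4 | 1.003 (4%) | 1.003 (5%) | 1.006 (4%) | 1.003 (5%) |

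R made up 76% to 78% of total PASI days and correlated 0.91 to 0.93 with the total.

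In the first four rows X acts only through remission, so a null result after adjustment follows from the set-up. The fifth row adds a direct effect on recurrence and is more informative. On the log scale, 3C keeps ln 1.031 / ln 1.249 = 0.0305 / 0.2223 = 14% of its effect, while 3D keeps ln 1.224 / ln 1.266 = 0.2021 / 0.2359 = 86%. The adjusted 3D value of 1.224 is close to the direct effect put in, exp(0.2) = 1.221. The joint model therefore estimates a direct effect properly; it is not the quantity that the hypotheses state.

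**5. T0 against Table 1.** The T0 column is filled only for the PP1 chart items, which include current and lifetime suicidality, psychiatric emergency and medication non-adherence. MADRS, YMRS, BAI, STAXI, CGI-S and EQ-5D first appear at T1 in the PP3 block. The S-STS first appears at T1 in the PP2 block; its PP3 row starts at T2.

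**The case against.** The joint model is the natural reading, but it is inferred. The text could be grouping hypotheses by type of method, and exact covariate sets are often left to an analysis plan that is not shown. The backward-selection analysis might also serve 3C and 3D, since the hypotheses call their factors moderators. This stands in part: the article does not rule out a separate model. But it names the outcome and the main regressor for each pair, and those words misdirect 3C. Backward selection is no remedy. Offered a regressor correlated about 0.9 with the outcome, it would be expected to keep that one and drop the baseline factors.

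A reader might infer that real risk factors would be reported as having no effect. The documents do not support that. It requires factors that act almost wholly through remission, whereas the article speaks only of possible correlates. The planned work on correlates of time to remission, and the comparison of faster and slower remitters, could still reveal such factors, although neither tests 3C or 3D as worded.

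A reader might also infer that 3D is affected as badly as 3C. That does not follow. The overlap with the outcome depends on a time origin that the article does not give, and with a direct effect on recurrence the loss in the illustration is modest.

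Mediators are a declared interest, so a conditional effect is a legitimate target. It is a second question, though, and mediation work also needs the total association. Finally, the article calls the study exploratory, and no data are lost whichever model is fitted. That lowers the severity without making the model answer the hypothesis.

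**Conclusion.** The point holds, most firmly for 3C. Followed as written, the count model conditions the baseline factors on a post-baseline intermediate that is also an additive part of total PASI duration, and so it does not estimate the association that 3C states. Under the assumed inputs, the rate ratio per SD falls from 1.15–1.38 to 1.00–1.02 when the factor acts only through remission, and from 1.25 to 1.03 (power 99% to 14%) when it also affects recurrence directly. The size depends on how much of each factor's effect runs through remission, which the documents do not tell us.

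For 3D the model also conditions on an intermediate, but the consequence may be small: hazard ratio 1.27 to 1.22 and power 79% to 67% in the direct-effect scenario.

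The T0 label conflicts with Table 1 for the rating scales only. It would be wrong to conclude that every factor should move to T1, because some chart items are recorded at T0.

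Severity: should be fixed. The analysis is declared hypothesis-generating and the appropriate models remain available from the same data.

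**What to change.** - **3C and 3D:** fit models with the prespecified baseline factors and the centre random effect, without time to remission. State the time origin for recurrence in the Cox model.
- **3A and 3B:** keep time to remission as the exposure here only, with the baseline factors as adjustment variables. Note that in 3A it is also part of the outcome, so some association is built in.
- **Joint model:** if one is shown, label it a secondary direct-effect or mediation analysis.
- **Backward selection:** say whether time to remission is a candidate, and exclude it where the result is meant to answer 3C or 3D.
- **Time points:** under *Aims and hypotheses*, give T1 for the rating-scale factors (MADRS, YMRS, BAI, STAXI, CGI-S, EQ-5D, S-STS) and keep T0 only for chart items recorded then.

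The cost is a few sentences and one additional model per outcome. No new data are needed and the sample size is unchanged.
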